# Cluster randomized controlled trial of a peer support program for people with diabetes: study protocol for the Australasian peers for progress study

**DOI:** 10.1186/1471-2458-12-843

**Published:** 2012-10-04

**Keywords:** Peer support, Diabetes, Self-management, Support group

## Abstract

**Background:**

Well managed diabetes requires active self-management in order to ensure optimal glycaemic control and appropriate use of available clinical services and other supports. Peer supporters can assist people with their daily diabetes self-management activities, provide emotional and social support, assist and encourage clinical care and be available when needed.

**Methods:**

A national database of Australians diagnosed with type 2 diabetes is being used to invite people in pre-determined locations to participate in community-based peer support groups. Peer supporters are self-identified from these communities. All consenting participants receive diabetes self-management education and education manual prior to randomization by community to a peer support intervention or usual care. This multi-faceted intervention comprises four interconnected components for delivering support to the participants. (1) Trained supporters lead 12 monthly group meetings. Participants are assisted to set goals to improve diabetes self-management, discuss with and encourage each other to strengthen linkages with local clinical services (including allied health services) as well as provide social and emotional support. (2) Support through regular supporter-participant or participant-participant contact, between monthly sessions, is also promoted in order to maintain motivation and encourage self-improvement and confidence in diabetes self-management. (3) Participants receive a workbook containing diabetes information, resources and community support services, key diabetes management behaviors and monthly goal setting activity sheets. (4) Finally, a password protected website contains further resources for the participants. Supporters are mentored and assisted throughout the intervention by other supporters and the research team through attendance at a weekly teleconference. Data, including a self-administered lifestyle survey, anthropometric and biomedical measures are collected on all participants at baseline, 6 and 12 months. The primary outcome is change in cardiovascular disease risk using the UKPDS risk equation. Secondary outcomes include biomedical, quality of life, psychosocial functioning, and other lifestyle measures. An economic evaluation will determine whether the program is cost effective.

**Discussion:**

This manuscript presents the protocol for a cluster randomized controlled trial of group-based peer support for people with type 2 diabetes in a community setting. Results from this trial will contribute evidence about the effectiveness of peer support in achieving effective self-management of diabetes.

**Trial registration number:**

Australian New Zealand Clinical Trials Registry (ANZCTR); ACTRN12609000469213

## Background

In most countries around the world, diabetes is now one of the leading chronic diseases; around 4.4% of Australians are already diagnosed with diabetes (types 1 & 2) in 2007–08 and this number is continuing to rise [1,2]. In 2003, diabetes was responsible for 5.5% of the total burden of disease in Australia, with 92% of this burden due to Type 2 diabetes (T2DM). People with diabetes are at significantly greater risk of serious complications such as heart attack, stroke, blindness, renal failure and lower-limb amputation [3]. Such complications more than double the cost of care [4].

Due to the chronic nature of diabetes, much of the disease management and glycaemic control needs to be self-managed. The person with diabetes is required to adopt and maintain lifestyle and behaviour changes related to diet and exercise, glycaemic control, medication and integration of clinical care; and collectively, these steps have been shown to reduce risk of diabetes complications [5]. People with diabetes require additional resources and support to facilitate and achieve these changes; and although social and emotional support can occur through family and friends, most people require additional supports as well [6], e.g., from peers.

Peer support refers to the provision of emotional, appraisal and informational support from people who have experiential knowledge of a condition [7]. This support functions to complement, supplement and extend formal primary care services. It relies on non-hierarchical, reciprocal relationships, which provide a flexible supplement to formal health services for people with a chronic disease [7]. In addition, peer support can also foster understanding and trust of health care staff among groups who otherwise may be alienated from or have poor access to health care.

As identified in a World Health Organization (WHO) Report [8] concerning peer support programs, more research is required to identify the key ‘active’ components of these programs and particular features which may contribute to better outcomes. A recent systematic review of peer-led chronic disease self-management programs concluded that such programs may lead to small, short term improvements in participants’ self-efficacy, self-rated health, cognitive symptom management, and frequency of aerobic exercise [9]. There remains a lack of evidence concerning medium and longer-term clinical and other outcomes and there is no unequivocal evidence concerning the long-term impact on appropriate use of health services.

Peers for Progress, a global initiative of the American Academy of Family Physicians Foundation (AAFPF) [10], was developed from a WHO consultation that was held to identify and accelerate global best practices in peer support for health [11]. This global initiative aims to strengthen evidence of the value of peer support through the funding of 14 “evaluation” grants around the world. The Peers for Progress program initially identified three core functions [12] and subsequently added a fourth [11,13] and these are:

i. *Assistance & consultation in applying a diabetes management plan in daily life* – (e.g. goal setting, problem solving, role play behaviours and trouble shooting)

ii. *Social and emotional support* – (e.g. encouragement, empathy, support & skills to deal with stress, simply “being there”)

iii. *Linkages to and assistance in gaining access to clinical care* – (e.g. promote importance of clinical care, encourage development of communication skills to enhance interaction with clinicians)

iv. *Ongoing support –* (e.g. flexible, proactive, as needed, continuing availability)

In spite of diversity of setting and model of peer support being implemented in each country, each of the current trials is evaluating the same four key functions in order to a) provide a template for global standardization and program coherence and, at the same time, b) encourage flexibility for local tailoring for local implementation [11,14].

As the largest non-governmental organisation responsible for diabetes in Australia, Diabetes Australia has representative organisations in each state and territory of the country. Diabetes Australia–Vic (DA–Vic) has been providing financial and technical assistance to an existing community network (ComNet) of peer support groups for people with diabetes for many years and there are over 60 groups throughout the state of Victoria. These groups provide information, resources and support for people with diabetes, their families and carers. A 2005 evaluation of the ComNet program [15] identified several ways in which this program might be further enhanced to improve access to educational resources, connections with local health services and group sustainability. Compared with professionally-led groups, where the focus may be purely education [6], and the unstructured and less formal untrained DA-Vic ComNet support groups, the Australasian Peers for Progress – Diabetes Project (Aust PfP-DP) aims to implement and evaluate peer led, group based peer support in which people with T2DM within a specified local community meet to share their self-management challenges, explore and develop strategies to overcome these challenges and sustain health behaviour change using the experiences and support of the group. This program emphasizes formalized training of voluntary lay supporters/group facilitators with ongoing support and a clear structure, which identifies active components and processes conducive to improving daily management of diabetes, positive behaviour change and linkage and access to clinical care.

## Methods/Design

### Study aims

The aim of this study is to implement and evaluate the extent to which the Aust PfP-DP improves diabetes control by the provision of:

i. Assistance and consultation in applying diabetes management plan in daily life;

ii. Social and emotional support;

iii. Linkages to and assistance in gaining access to clinical care; and

iv. Ongoing availability of support

The primary outcome is cardiovascular disease (CVD) risk using the UK Prospective Diabetes Study (UKPDS) risk equation [16]. We hypothesize that participants receiving the peer support intervention will achieve a significantly greater reduction in CVD risk. Secondary outcomes include biomedical, quality of life (QoL) and psychosocial functioning, physical activity, medication adherence, nutrition and BMI. We hypothesize these secondary measures will be significantly improved at 12 months following baseline measurement in those receiving peer support intervention, compared with those not receiving the intervention. Furthermore, we will evaluate the cost-effectiveness of the program.

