### Study design and setting

The study is a cluster randomized controlled evaluation of a group-based peer support program, implemented and reported in accordance with the requirements of the CONSORT statement [17] and its extension to cluster randomized trials [18]. The study is being conducted in Victoria, Australia, a state that is divided into 79 local government areas (LGAs) within five regional and three metropolitan health regions. Community (defined as a post code area) peer support groups consisting of 10 – 12 participants are recruited, undergo baseline assessment, and then all participants are offered the opportunity to attend a one day diabetes self-management education (DSME) program to ensure that the intervention group does not simply use the sessions to obtain diabetes education rather than peer support. Finally, the groups are randomized to either an intervention arm or usual care arm with group postcode location being the unit of randomization. Groups assigned to the intervention arm participate in the peer support program for 12 months, while those assigned to the control arm continue with their usual care. Figure 1 is a CONSORT diagram of the study design. 

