### Sample size calculations

Sample size was determined by a requirement to have sufficient power to detect a meaningful difference between intervention and control group means of participant UKPDS score changes from baseline to 12 months. During the study, both groups will age by 1 year, which will increase their UKPDS risk calculation by identical amounts [16]. We anticipate this increase would be offset by reductions due to improvements in systolic blood pressure, total cholesterol/HDL cholesterol ratio, HbA_1_C, or smoking status. Assuming a standard deviation of 5% in baseline to 12 month UKPDS changes in both groups, 100 individuals per study arm with 12 month follow-up are required to provide 80% power to detect, with a 2 sided p-value of 0.05 for significance, a mean reduction of cardiovascular risk in the peer support arm that is 2% greater than any mean reduction in the usual care arm. The clustering of individuals by actual peer group (intervention arm) or future group (usual care arm) was not adjusted for because the comparisons across clusters are within-person changes over time and previous studies of UKPDS change in similar clusters found no clustering effects. Hence 12 groups and 120 participants per arm are required at baseline.

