### Allocation

Upon completion of recruitment (participant and peer supporter), DSME and baseline measurement, groups are randomized in each health region (comprising 2 or 4 groups) so that each health region contained an equal number of intervention and usual care groups. Allocation to intervention or usual care was governed by a random number generation process using Stata statistical software, Release 11.

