### Peer supporter training & support

Suitable peer supporters from locations randomized to the intervention arm are trained over two and a half days by a credentialed diabetes nurse educator experienced in group facilitation training. Peer supporter training aims to equip supporters with communication and group facilitation skills to help them support their group members to tell their stories, set goals, problem solve, increase awareness and linkages with the available health system, optimize self-management behaviours, including glucose monitoring, dietary changes and physical activity, as well as provide emotional support. The work with the research team with respect to data collection including reports of group meetings and individual contacts is reviewed and explained during the training. Additionally, peer supporters are invited to assist with scheduling meetings and to locate potential venues for group meetings within their communities.

Peer supporters are supported during the intervention period through weekly teleconferences with the project and specialist staff including diabetes educators, dieticians and psychologists. Furthermore, peer supporters receive a weekly informational e- newsletter about aspects of diabetes care and self-management, additional information in response to questions from group members and information they might share with their group members as well as reminders about joining the teleconference the following week and minutes from the preceding teleconference (Figure 3). Peer supporters are asked to attend at least one teleconference each month. These calls, which are recorded, emulate a supportive peer group meeting in that discussion and conversation with the project staff will provide organisational and informational support and the supporters provide experiential, emotional and social support to each other. During these teleconferences, supporters review their group meetings, discuss important events, share stories, ask questions on behalf of their group members and receive support from their peers.

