### Data collection and outcome measures

Baseline data collection is completed prior to randomization and is accomplished by a self-administered survey, anthropometric measurements collected by the study team or obtained from the participant’s clinical care provider as well as blood and urine analysis, specifically for the study or from a recent test requested by the clinical care provider. Table 1 shows the measurement tools used for data collection, the method of collection and time points (baseline, six or 12 months) at which data is collected. Anthropometric measures are collected by project staff specifically trained in accordance with standard clinical measurement methods [21]. Briefly, the left arm circumference is measured to determine the appropriate cuff size for blood pressure (BP) measurement. BP and pulse is measured and recorded three times using the Omron HEM-907 IntelliSense professional digital blood pressure monitor with at least one minute between readings. Height is measured using a portable stadiometer height rod to the nearest 0.5 cm whilst the participant is standing without shoes. Weight is measured to the nearest 0.1kg using a Salter portable weighing scale, model 913. Waist circumference is measured halfway between the lowest rib and the top of the hipbone using the Novel figure finder tape measure. Duplicate waist circumference measurement is undertaken for approximately 10% of the participants for quality assurance. Blood pressure machines and weight scales are calibrated at least weekly. Pathology laboratories providing blood and urine analysis are accredited by the National Association of Testing Authorities (http://www.nata.asn.au/) and all methods for determining HbA1c% are NGSP approved (http://www.ngsp.org/). 

**Table 1 T1:** Measurement domains, survey tools and collection method used at each data collection time point

**Variable**	***Component***	**Measurement tools/Questions**	**Base line**	**6 mth**	**12 mth**	**Type of administration**
Demographic Measures		Age at diagnosis	✓	✓		
		Health Insurance	✓		✓	Postal survey
		Age, Sex, Country of birth, Living Arrangement (Marital status), Education, Income, Employment status,	✓		✓	
		Ethnicity, Health Care Access,	✓		✓	
Clinical Information	*Current Clinical Measures*	On insulin, since when, #/day, Most recent HbA1c,	✓	✓	✓	
		Other medical treatments, past medical history	✓		✓	Postal survey
		List of prescribed medications, last dilated eye				

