Cost Effective Analysis		# visits past 6 mths to diabetes clinician	✓	✓	✓	Postal survey
		# visits past 6 mths to other clinicians	✓	✓	✓	
		# visits past 6 mths for emergency/acute care	✓	✓	✓	
		# overnight stays past 6 mths in hospital (related to your diabetes)	✓	✓	✓	
Peer Training/ Quality Improve.	*Training effectiveness*	Usefulness of training		✓	✓	Postal survey
		Extent of content covered				
Process Evaluation		17 item assessment with 3 additional questions regarding most helpful, least helpful and suggestions to improve		✓	✓	Postal survey
		+ 2 questions asking availability of participant to other group members [38-40]				

The primary outcome measure is cardiovascular disease (CVD) risk using the UKPDS risk calculation [16]. People with diabetes are already at higher risk of CVD than the general population without diabetes. We consider that a 10% reduction in risk will be clinically significant, if we assume that the average risk for our participants is likely to be 20 – 25% in line with that in a sample with type 2 diabetes from Australian general practice [41]. Age at diagnosis, sex, ethnic group, smoking status, HbA1c, systolic blood pressure and total cholesterol/HDL ratio will be used in the UKPDS equation to determine CVD risk at baseline and 12 months [16]. Changes in the CVD risk over time as well as changes in waist circumference, body mass index (BMI), weight, and lipid profile will be used to assess diabetes self-management post intervention. Quality of life (AQoL [27] & EQ-5D[28,29]), depression (PHQ9, [32]) diabetes distress screening [30,31], self-care activities [23,24], medication adherence [25,26], food, smoking and alcohol intake [22], current support systems [34], known co-morbidities associated with diabetes, utilization of and satisfaction with available health services [37], diabetes knowledge using the Michigan Diabetes Research and Training Center Brief Diabetes Knowledge Test with modification to Australian context [35], health literacy [33] and confidence of diabetes management [36] are measured at baseline, six and 12 months.

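### The 12-month assessment is counted from baseline, but the 12-month programme starts later by an unstated lag, so the plan does not ensure a post-intervention outcome

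*Protocol article*

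**What the plan says.** **Outcome clock.** In the Protocol article, Study aims, the secondary outcomes are expected to be "significantly improved at 12 months following baseline measurement in those receiving peer support intervention". The primary hypothesis in that section carries no time point. Its clock comes from Sample size calculations, which compares "means of participant UKPDS score changes from baseline to 12 months" and adds: "During the study, both groups will age by 1 year".

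**Order of events.** Data collection and outcome measures states: "Baseline data collection is completed prior to randomization". Study design and setting has groups "undergo baseline assessment, and then all participants are offered the opportunity to attend a one day diabetes self-management education" (DSME) and randomises them last. Allocation makes randomisation wait for whole regions of 2 or 4 groups: "Upon completion of recruitment (participant and peer supporter), DSME and baseline measurement, groups are randomized in each health region". Training follows allocation: "Suitable peer supporters from locations randomized to the intervention arm are trained over two and a half days".

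**Programme length.** Study design and setting gives intervention groups 12 months of programme once assigned. The Abstract describes 12 monthly meetings led by supporters who have been trained.

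**Label on the result.** Data collection and outcome measures says that changes in CVD risk, together with waist, BMI, weight and lipid changes, "will be used to assess diabetes self-management post intervention".

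**The concern.** Three statements do not fit together if each is taken at its word: the outcome is read 12 months after baseline; a 12-month programme starts some time after baseline; and the reading is taken after the intervention. With any positive lag between baseline and programme start, the third is untrue of the full programme.

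What is at stake is the question the trial answers. People measured first in a region wait longest for randomisation, so time in the programme at the 12-month visit would vary by person and by region, and the article states no rule that controls it. Less exposure at assessment could dilute the effect. The trial-based economic evaluation, which takes costs and outcomes as they occur in the trial, could set the cost of a full programme against an effect read before its end. At the 6-month visit, the service-use questions covering the previous six months would include time before randomisation.

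**Working it through.** **1. The plan's own figure.** Inputs from Sample size calculations: difference 2 points, SD 5, two-sided alpha 0.05, power 80%.

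- n per arm = 2 × (1.960 + 0.842)² × 5² / 2² = 98.1, rounded up to 99. The t-test version gives 99.1, hence 100.
- Power with 100 per arm is 0.807 (normal approximation) or 0.804 (t-test).
- 120 at baseline corresponds to a loss of one sixth: 100 / (1 − 1/6) = 120.

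The stated sample size reproduces and is not in dispute.

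**2. Timing.** Let L be the months from baseline measurement to the first meeting, and let that meeting open the programme. The documents do not give L, so a range is shown.

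- Meeting k falls at month L + k − 1, so meeting 12 falls at month L + 11.
- A 12-month programme ends at month L + 12.
- Meetings held by month 12 = min(12, floor(12 − L) + 1).

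| L (months, assumed) | Meeting 12 at month | Programme ends at month | Meetings held by month 12 |
|---|---|---|---|
| 0 | 11 | 12 | 12 |
| 0.5 | 11.5 | 12.5 | 12 |
| 1 | 12 | 13 | 12 |
| 2 | 13 | 14 | 11 |
| 3 | 14 | 15 | 10 |
| 4 | 15 | 16 | 9 |

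For every L above zero the 12-month programme is unfinished at the visit. Meetings are lost only when L exceeds one month. The first to go is meeting 12, which Intervention condition identifies as one of only two meetings whose content is not flexible.

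**3. Is L above zero?** The stated order implies it. After baseline come the education day (offered at ten locations across the state), completion of all preparatory steps in the region, randomisation, and two and a half days of supporter training. Its size cannot be derived from the article.

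**4. Illustration of dilution.** Two assumptions outside the documents are needed: that the planned 2 points are the effect of the complete programme, and that the effect accrues in proportion to exposure. With SD 5 and 100 per arm, the standard error is 5 × √(2/100) = 0.707 and power ≈ Φ(difference / 0.707 − 1.96).

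| L | Difference if proportional to time, 2 × (12 − L)/12 | Power | Difference if proportional to meetings held | Power |
|---|---|---|---|---|
| 1 | 1.83 | 0.737 | 2.00 | 0.807 |
| 2 | 1.67 | 0.654 | 1.83 | 0.737 |
| 3 | 1.50 | 0.564 | 1.67 | 0.654 |
| 4 | 1.33 | 0.470 | 1.50 | 0.564 |

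The two columns differ by seven to nine percentage points of power at the same lag. That shows how far the result depends on the assumed accrual.

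**The case against.** The strongest case against is that 6 and 12 months are nominal visit labels. The sentence in Study aims is a hypothesis about the secondary outcomes, and no section says that visits are scheduled from each person's own baseline date. Visit windows are operational detail that a full protocol may hold, and the study-design diagram is not shown. Allocation also lists baseline measurement among the steps completed just before randomisation, and training is short, so the lag may be small. This stands in part: the size of the lag is unknown. It does not remove the mismatch, because the baseline anchor is written down for both the secondary and the primary outcome and is not merely left out.

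Three stronger readings are tempting, and the documents do not support them.

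- A reader might infer that the visit must fall before the twelfth meeting. With a lag of one month or less, all twelve meetings can be held by month 12.
- A reader might infer a definite loss of power. Sample size calculations defines the 2-point difference at the 12-month assessment itself, not as the effect of a completed programme. Neither the lag nor the way the effect builds up is given.
- A reader might infer that the arms are followed for different lengths of time. Usual care gives control participants the same baseline, 6- and 12-month measurements, and nothing plans to delay the visit in one arm only.

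**Conclusion.** The point holds as an inconsistency in timing. A visit 12 months after baseline precedes the end of a 12-month programme by exactly the baseline-to-start lag, so the text does not secure the post-intervention status that it claims. The programme is incomplete at the visit for any positive lag. The meeting count falls short only for lags above one month (11 of 12 at 2 months, 10 of 12 at 3).

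The consequence is shorter and variable exposure at assessment, which could dilute the estimated effect. While both arms share one clock it is not bias between arms. The power figures above illustrate sensitivity and are not an estimate for this trial. The conclusion rests on reading the baseline anchor literally and on the first meeting opening the programme. It is a worthwhile, low-cost improvement and not a flaw that invalidates the comparison.

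**What to change.** Reconcile Study aims, Study design and setting, Sample size calculations, and Data collection and outcome measures on one clock. Time the 6- and 12-month assessments in both arms of each health region from one common post-randomisation date: either randomisation or the region's planned programme start. Planned start matches the post-intervention label more closely, since supporter training still follows randomisation. Use the same calendar window for the region's control groups, and report the baseline-to-randomisation interval by arm.

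The cost is rescheduling of visits already planned, with none added. The interval from baseline will exceed 12 months by the lag. The common regional date applies equally to both arms and baseline dates precede allocation, so the excess should be alike between arms; the reported interval allows this to be checked. The statement in Sample size calculations that both groups age by one year becomes approximate. In four-group regions the two intervention groups may start on different dates, so a single regional date reduces variation in exposure but need not remove it.
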